## Abstract

**Background:**

Atrial fibrillation is common in patients with structural heart disease who are undergoing cardiac surgery. Surgical CryoMaze has been shown to be an effective treatment in several trials, but success rates have varied considerably, between 47–95 %. The sequential hybrid approach, combining surgical CryoMaze followed by radiofrequency catheter ablation, can achieve high freedom from atrial arrhythmias, even when rigorous methods to detect arrhythmias after the procedure are used. However, data from randomized trials comparing hybrid ablations to surgical ablations alone are lacking.

**Methods/Design:**

The SurHyb study is a prospective, multicenter, randomized study. Patients with persistent or long-standing persistent atrial fibrillation will be randomized to either surgical CryoMaze alone or surgical CryoMaze followed by catheter ablation 3 months post-surgery. The primary outcome measure is arrhythmia-free survival without class I or III antiarrhythmic drugs, which will be evaluated using 7-day ECG Holter monitoring at 24 months. A total of 260 patients will be investigated from three medical centers in the Czech Republic to obtain the relevant information.

**Discussion:**

This is the first randomized study that compares surgical CryoMaze alone with the staged hybrid surgical CryoMaze followed by catheter ablation in patients with persistent or long-standing persistent atrial fibrillation. These results will contribute to the optimization of the treatment for these patients.

**Trial registration:**

Czech Clinical Trials Registry, cz-301020151253. Registered on 30 October 2015.

## Background

Atrial fibrillation (AF), the most common clinically significant cardiac arrhythmia, is associated with increased mortality and morbidity [1]. The incidence of AF will continue to increase due to aging of the population. In patients indicated for cardiac surgery, the prevalence of AF is higher compared to the general population [2], and it can be as high as 50 % in individuals with mitral valve disease [3].

Both surgical and catheter ablation have become recognized treatments for symptomatic and drug-refractory AF. The CryoMaze ablation procedure was developed as a surgical alternative to cut-and-sew procedures as a way to decrease invasiveness [4]. A variety of surgical ablation energy sources have been used including microwaves, laser, and unipolar or bipolar radiofrequency energy. The CryoMaze operation is usually done in conjunction with a coronary bypass operation, valve surgery, or other open heart surgery. Incomplete lines after surgical ablation are common and can be pro-arrhythmic [5, 6]. The efficacy of the CryoMaze procedure as the sole treatment for persistent AF has been shown in several studies, but the results are hindered by small patient numbers and less than accurate follow-up assessments of heart rhythm, such as via telephone interviews with only occasional use of continuous electrocardiographic (ECG) recordings [4, 7]. This has led to mixed results, with rates of freedom from AF being reported between 47–95 % [8, 9]. Additionally, the need for subsequent transvenous catheter procedures remains unknown; also, the clinical procedures employed varied between centers.

In a non-randomized study, sequential surgical CryoMaze procedures followed by catheter ablation led to high freedom from arrhythmia in patients with persistent and long-standing persistent AF and without an increase in complications [10]. However, there have been no randomized clinical trials conducted to evaluate whether the hybrid approach is superior to a CryoMaze procedure alone; therefore, a recommendation regarding the best procedure for all patients is unavailable.

The aim of this randomized, multicenter clinical trial is to compare clinical efficacy and safety of the staged hybrid ablation to a CryoMaze procedure alone in a well-described population of patients with AF.

## Methods

The Sequential Hybrid Surgical CryoMaze Ablation versus Surgical CryoMaze Alone for the Treatment of Atrial Fibrillation (SurHyb) study was designed to be a prospective, randomized multicenter study. Patients will be recruited from three major cardiovascular centers in the Czech Republic (South Bohemia Cardiac Centre in Budweis, the Institute for Clinical and Experimental Medicine in Prague, and Na Homolce Hospital in Prague). Patients will be approached during the clinical review before the surgical operation and will be offered an opportunity to participate in the study. There will be a follow-up period of 2 years for each enrolled patient. The objective of the study is to compare a staged hybrid surgical cryoablation, followed 3 months later by catheter ablation, to a surgical CryoMaze alone. A flowchart of the SurHyb trial is shown in Fig. 1. Written informed consent will be obtained from all patients prior to the study. All participating centers will have an appointed local investigator who will be responsible for appropriate inclusion and follow-up of patients. The trial sponsor is the South Bohemia University in Budweis. The regulations regarding medical confidentiality and data protection are fulfilled.

**Fig. 1 Fig1:**
[figure not shown]
SurHyb study flowchart

### Inclusion and exclusion criteria

All patients need to meet the following inclusion criteria:Cardiac surgery (either valve operation or coronary artery bypass grafting or combination of both) with concomitant CryoMaze ablation as a treatment for persistent or long-standing persistent AFAt least one failed class I or III antiarrhythmic drugAge ≥18 yearsWilling to sign the informed consent formSymptomatic persistent or long-standing persistent AF documented using electrocardiography; symptoms may include, but are not restricted to, palpitations, shortness of breath, chest pain, fatigue, left ventricular dysfunction, or any combination of theseAble and willing to comply with all pre-, post-, and follow-up testing and requirements

The exclusion criteria are as follows:Permanent and paroxysmal AFPrevious surgical or catheter ablation for AF (does not include ablation for atrial flutter or other supraventricular arrhythmia)Clinically estimated life expectancy of 5 years or less or mental and/or physical inability to comply with the follow-up periodArrhythmia secondary to a reversible or non-cardiac causeSerious liver or renal dysfunction (alanine aminotransferase [ALT] >80 U/l, aspartate aminotransferase [AST] >80 U/l, creatinine >132 μmol/l)Pregnancy or the possibility of pregnancy, or breast feedingAge younger than 18 yearsContraindication to systemic anticoagulationEnrollment in an experimental study evaluating another device or drug under investigationPatient not competent to legally represent him or herself (e.g., requires a guardian or caretaker as a legal representative)

### Screening and enrollment

Approximately 600 patients per year are scheduled for cardiac surgery with concomitant CryoMaze ablation in all three cardiovascular centers involved in the study. The patients who fulfill the inclusion criteria will be approached by the local investigator, who will explain the SurHyb study and provide a patient information form. We expect that 50–70 % of eligible patients will consent.

### Randomization

The SurHyb study is a prospective, randomized, multicenter study. After providing informed consent, patients will be randomly assigned using a computer system to one of the two groups — the hybrid group or the surgery alone group — initially in a 1:1 ratio. The surgeon will be blinded as to the treatment group until the surgery is completed. All patient data will be collected using a standard form and transmitted to a central database.

### Interventions

The study consists of two study arms: the *hybrid group*, which will receive surgical CryoMaze followed, in 3 months, by catheter ablation in all patients, or the *surgical CryoMaze group*, in which participants will receive surgical cryoablation with no planned catheter ablation after discharge.

### Primary outcome measure

The primary outcome measure is arrhythmia-free survival without class I or III antiarrhythmic drugs, which will be evaluated using a 7-day Holter monitoring at 24 months. After a 3-month blanking period, if a patient requires a repeat ablation, cardioversion, or antiarrhythmic drugs, this will be considered as a failure.

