### Follow-up

Clinical follow-up will be performed at 3, 6, 12, 18, and 24 months after the index procedure (surgical ablation in the surgical cryoablation group and catheter ablation in the hybrid group). Seven-day Holter monitoring will be performed before each follow-up in all patients. The absence or presence of atrial tachyarrhythmias on the ECG Holter will be assessed, and any need for additional ablation procedures, antiarrhythmic drugs, or cardioversions after the blanking period will be considered as a failure. Clinical status, medication, blood pressure, 12-lead electrocardiogram, and any adverse events will be documented during every visit. Unless necessary, antiarrhythmic drug therapy will be discontinued at the first follow-up visit. Medical records will be reviewed at each visit to determine the moment of antiarrhythmic medication changes.

An echocardiogram will be performed within 1 week following the surgical ablation or, if performed, within 1 week after the catheter ablation. Further echocardiograms will be performed at the 12 and 24 month follow-ups. Left atrial size will be determined using the long-axis parasternal view and the apical two-chamber view. In addition, the left ventricular end systolic and the left ventricular end diastolic diameter will be measured, and diastolic function will be assessed by computing the ratio of early to late diastolic filling, the E/A ratio.

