### Sample size calculation

Power calculations to provide estimates for the necessary sample size were conducted concerning recurrence rates of AF or atrial tachycardia episodes at 24 months as the primary outcome endpoint. The clinical efficacy of the hybrid ablation procedure was assumed to be 86 %, whereas the efficacy of the surgical ablation alone was assumed to be 50–70 %. To ensure 80 % power of the Fisher exact test at the 5 % significance level, a sample size of at least 130 must be included in each of the trial arms. Considering a dropout rate of 20 %, approximately 170 patients will finally be recruited for each trial arm. At the end of the study, the number of patients free from arrhythmias should be similar in both groups, but the proportion of those submitted to another procedure, commenced on antiarrhythmic drugs, or undergoing cardioversion should differ significantly.

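### A post-blanking drug, cardioversion or repeat ablation is a primary failure without any documented arrhythmia, and the clinicians who decide on these treatments can know the arm

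*Protocol article*

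**What the plan says.** Under Primary outcome measure, success is arrhythmia-free survival off class I and III drugs, judged on a 7-day Holter at 24 months. Treatment counts against the patient as well: "After a 3-month blanking period, if a patient requires a repeat ablation, cardioversion, or antiarrhythmic drugs, this will be considered as a failure". The Follow-up section repeats the rule beside the Holter assessment: "any need for additional ablation procedures, antiarrhythmic drugs, or cardioversions after the blanking period will be considered as a failure". Neither section asks for a tracing before the treatment or says what establishes the need.

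For drugs, Follow-up sets a default with an exception: "Unless necessary, antiarrhythmic drug therapy will be discontinued at the first follow-up visit".

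Under Randomization, the one statement on blinding is "The surgeon will be blinded as to the treatment group until the surgery is completed". Interventions gives the staged catheter procedure to the hybrid arm only.

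Sample size calculation closes with an expectation in two halves. At the end of the study, "the number of patients free from arrhythmias should be similar in both groups", while "the proportion of those submitted to another procedure, commenced on antiarrhythmic drugs, or undergoing cardioversion should differ significantly".

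Two other passages bear on the point. Surgical ablation says that a surgery-alone patient in persistent AF after the 3-month blanking period is cardioverted, and that this is not a failure if sinus rhythm holds. Secondary outcome measures lists arrhythmia-free survival irrespective of drugs and re-do ablation, and counts of cardioversions and re-do ablations.

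**The concern.** Three features act together.

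- A treatment decision is a failure whatever the rhythm record shows.
- The person deciding can know the arm. Hybrid patients have a further admission and a catheter procedure in which the surgical lines are checked and gaps closed; surgery-alone patients do not.
- The article itself expects a significant difference in these treatment components.

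A clinician may be readier to stop a drug after the lines have been checked by catheter, and readier to continue it where no further procedure is planned. A patient with clean Holters who is kept on a class I or III drug is then a primary failure. If this happens more often in one arm, a difference in prescribing enters the primary comparison as a difference in efficacy. At stake is whether a significant primary result can be read as prevention of arrhythmia.

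**Working it through.** **Inputs from Sample size calculation.** Hybrid success 86%; surgery-alone success 50–70%; Fisher's exact test at 5% (taken as two-sided, since the article does not say); 80% power; at least 130 per arm.

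**The plan's own figure.** At the most demanding contrast, 86% against 70%, exact enumeration of the two-sided Fisher test gives 80% power at about 114 per arm and 85.5% power at 130. The 130 is not reproduced, but it errs on the safe side and does not affect this point. I use 130 as the evaluable number per arm.

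**Model for the illustration.** Both arms have the same true success rate p. In the surgery-alone arm, an extra fraction d of all patients is counted as failed only because of a treatment decision:

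- hybrid successes ~ Binomial(130, p)
- surgery-alone successes ~ Binomial(130, p − d)
- P(significant for hybrid) = sum of the joint probabilities over all tables with Fisher p < 0.05 and more hybrid successes

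The values of d are assumptions; the article gives none. The common base p = 86% is also an assumption for the surgery-alone arm, so p = 70% is shown as well.

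| Assumed excess d | Surgery-alone rate, p = 86% | P(significant for hybrid) | Surgery-alone rate, p = 70% | P(significant for hybrid) |
|---|---|---|---|---|
| 0 | 86% | 1.7% | 70% | 1.8% |
| 5 points | 81% | 15% | 65% | 11% |
| 10 points | 76% | 48% | 60% | 34% |
| 15 points | 71% | 81% | 55% | 66% |

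With no excess and p = 86%, the test rejects in either direction in 3.3% of trials; the half that favours hybrid is 1.7%.

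**Same check on another scale.** Let q be the share of arrhythmia-free surgery-alone patients who are failed by treatment alone, so that their rate is p × (1 − q). At p = 86%:

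- q = 5%: 0.86 × 0.95 = 81.7%, significant for hybrid in 12% of trials
- q = 10%: 0.86 × 0.90 = 77.4%, 38%
- q = 15%: 0.86 × 0.85 = 73.1%, 69%

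**In patients.** If hybrid has 112 successes of 130, surgery alone reaches significance at 98 of 130. That is 112 − 98 = 14 patients, or 14/130 = 10.8 points.

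**In context.** The smallest effect the plan assumes is 86 − 70 = 16 points. An excess of 10 to 15 points would be most of that.

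**Direction.** The model puts all the excess in one arm. With the excess in the hybrid arm, the same probabilities apply in favour of surgery alone. The cardioversion exemption under Surgical ablation is written for surgery alone only, and it spares that arm some failures.

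**The case against.** The strongest reply is that these treatments mostly follow real recurrences. The text speaks of treatment that is required or needed, the drug default in both arms is to stop, a 7-day Holter precedes every visit, and cardioversion and re-ablation normally imply an arrhythmia. This largely stands for the two procedures and narrows the concern mainly to drugs. It does not remove it, because need is not tied to a tracing.

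A reader might infer from the end of Sample size calculation that the whole expected effect lies in discretionary decisions. The article does not establish that. The sentence can mean rhythm at month 24 after re-treatment, with the extra treatments partly reflecting true recurrences. The Discussion draws a similar distinction: 86% freedom at 12 months, against 94% when drug use or a successful re-do does not count as failure. Statistical methods and Sample size calculation also describe the primary comparison as recurrence of AF or atrial tachycardia.

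A reader might also infer that a positive result could not be told apart from bias. That goes too far: the rhythm-only secondary outcome and the treatment counts would help to show where a difference arose. Being secondary, they do not protect the primary test.

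Nor does it follow that treatment without a tracing should become a primary success. That would contradict an endpoint defined off class I and III drugs, could count drug-suppressed arrhythmia as success, and would depart from the definition behind the 86%.

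Finally, coded Holter reading may be in the full protocol, and its absence from the article is no defect. It would not by itself change failures that are triggered by treatment.

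**Conclusion.** The point holds as a weakness in the endpoint definition that should be fixed. As written, arm-aware treatment decisions, chiefly drug continuation, can create primary failures with no recorded arrhythmia, and the plan expects a significant difference in these components. Under the assumed excesses of 5 to 15 points in the surgery-alone arm, a significant result for hybrid without any true difference has a probability of about 15% to 81% from an 86% base, or 11% to 66% from a 70% base. With no excess it is below 2%. These figures rest on 130 evaluable patients per arm, a two-sided test and an excess confined to one arm. They show how sensitive the result is; they do not forecast bias. The article supports neither a particular size nor a certain direction.

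**What to change.** Keep the off-drug primary endpoint and make the source of each failure visible.

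1. For every treatment-based failure, record the date and source of any preceding post-blanking ECG or Holter tracing of atrial tachyarrhythmia. Report failures without a tracing by arm.
2. Prespecify a sensitivity analysis that counts a drug, cardioversion or repeat ablation as failure only when such a tracing precedes it. State that the primary conclusion will be read alongside this analysis and the rhythm-only secondary outcome.
3. Have the already scheduled Holters and the triggering tracings read under a code, without arm or procedure dates, by existing readers at another participating centre. If the full protocol already provides for this, nothing need be added.
4. Reconcile the cardioversion exemption for the surgery-alone arm under Surgical ablation with the failure rules under Primary outcome measure and Follow-up.

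The cost is one data field, one extra analysis and the exchange of recordings between centres. Since Data management gives each centre only its own part of the study website, that exchange needs an access arrangement. Patient care does not change as a result of items 1 to 3. Recruitment is still under way, so all of this can be settled before the final analysis.

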### Secondary outcome measures

The secondary outcome measures involve arrhythmia-free survival without class I or III antiarrhythmic drugs and without a need for repeat ablation or cardioversion, evaluated using a 7-day Holter monitoring at 6, 12, and 18 months. The measures include:Arrhythmia-free survival regardless of antiarrhythmic drugs status or re-do ablationsNumber of cardioversionsNumber of re-do ablationsFrequency and duration of hospital admissions for recurrent arrhythmiasFrequency and description of any procedure-related complications (during both surgical and catheter ablation)Cardiovascular mortality and morbidityChanges of left atrial dimension as measured using ultrasound echocardiography

### Anticoagulation therapy before ablation

Patients on warfarin, apixaban, dabigatran, or rivaroxaban will stop the medication and switch to either unfractionated or low molecular weight heparin, which will be maintained during the surgical procedure. Novel oral anticoagulants can only be used in accordance with current recommendations during the trial [11]. If the patient is taking only aspirin, it may or may not need to be discontinued.

### Surgical ablation

The CryoMaze ablation will be performed as an adjunct to a coronary artery bypass, valve surgery, or a combination of both. It will be done using the standard sternotomy approach, and each lesion will be created by an application of cryothermia at a fixed temperature. The target temperature, duration of application, and location of each lesion will be recorded. The standard minimum CryoMaze protocol will consist of continuous lesions surrounding each group of right and left pulmonary veins with linear lesions between the superior and inferior pulmonary veins with the aim of creating a box lesion. Other lines can be created at the surgeon’s discretion. The left atrial appendage will be excluded in patients with a previous history of stroke or a CHA_2_DS_2_-VASc score ≥2. All patients who remain in AF after the surgical procedure is completed will undergo attempted cardioversion before chest closure and again before hospital discharge if the arrhythmia persists. Patients will be left on their current antiarrhythmic medication covering the 3-month blanking period to avoid early recurrences, with the aim of discontinuing the medication at the first follow-up visit. Recurrences of AF, atrial tachycardias, or atrial flutter during the first 3 months may require a change of the antiarrhythmic medication or direct current cardioversion, but this will not be counted against the primary or secondary endpoints. The patients will continue with the same anticoagulation therapy after the operation unless a change in the medication has been required during the admission (e.g., anticoagulation for a newly implanted artificial valve or discontinuation of anticoagulation for severe bleeding). A 7-day ECG Holter monitor will be scheduled 3 months after surgery (just before admission for the catheter ablation in the hybrid group). If a patient in the surgical cryoablation group is in persistent AF after the 3-month blanking period, the patient will receive direct current cardioversion, and if he or she remains in normal sinus rhythm, this will not be considered a failure.

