### Catheter ablation

Patients randomized to the hybrid treatment arm will be admitted for a staged catheter ablation treatment 3 months after the CryoMaze procedure. In general, patients will continue with warfarin or stop one of the novel anticoagulation drugs 24–48 hours before the planned procedure (unless the surgeon decides otherwise). Electro-anatomical mapping of the left and right atria will be performed using a CARTO navigation system. First, an anatomical map will be created to provide a first look at the actual locations of the CryoMaze ablation lines (regions with voltage <0.1 mV). Pulmonary vein isolation will be confirmed by the absence of signals recorded using a multielectrode circular catheter. Completeness of all linear lesions created during the surgical CryoMaze will be confirmed by a bidirectional conduction block across the relevant line. Any gaps will be re-ablated using radiofrequency catheter ablation. If the patient is in atrial tachycardia at the beginning of the procedure, the tachycardia will be mapped and ablated as the first step. If the patient is in AF, an external electrical cardioversion will be performed during the procedure to restore sinus rhythm. The investigator can then add any of the current ablation methods including substrate modification or ablation of triggers induced by an isoproterenol infusion. Inducibility of AF or atrial tachycardia at the end of the procedure will be recorded. Patients will be discharged on their current antiarrhythmic medication for the 3-month blanking period with the aim of discontinuing the medication at the first follow-up visit. Any atrial tachyarrhythmias that may occur during the blanking period after the catheter ablation may require a change of the antiarrhythmic medication or external cardioversion. Intravenous heparin will be administered during the procedure, and warfarin will continue post-operatively with a target international normalized ratio between 2.0 and 3.0. Alternatively, novel oral anticoagulants, such as dabigatran, apixaban, or rivaroxaban, will be prescribed for a period of at least 3 months.

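### A control-arm cardioversion at the end of blanking is a failure under the outcome definition but may be exempt under the surgical section, so the same patient can be scored both ways and a later relapse has no fixed event date

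*Protocol article*

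**What the plan says.** All references are to the protocol article.

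- **Primary outcome measure:** "After a 3-month blanking period, if a patient requires a repeat ablation, cardioversion, or antiarrhythmic drugs, this will be considered as a failure". No exception is stated and none is cross-referenced.
- **Follow-up:** "any need for additional ablation procedures, antiarrhythmic drugs, or cardioversions after the blanking period will be considered as a failure". This covers all patients.
- **Secondary outcome measures:** the 6-, 12- and 18-month version must also be met "without a need for repeat ablation or cardioversion, evaluated using a 7-day Holter monitoring at 6, 12, and 18 months".
- **Surgical ablation:** the condition is "If a patient in the surgical cryoablation group is in persistent AF after the 3-month blanking period"; the consequence stated for such a patient is "the patient will receive direct current cardioversion, and if he or she remains in normal sinus rhythm, this will not be considered a failure". This concerns the surgery-alone arm only.
- **Hybrid arm, under Catheter ablation** (3 months after surgery): "If the patient is in AF, an external electrical cardioversion will be performed during the procedure to restore sinus rhythm". A further blanking period follows: "Any atrial tachyarrhythmias that may occur during the blanking period after the catheter ablation may require a change of the antiarrhythmic medication or external cardioversion".
- **Follow-up, index procedure:** the clock starts at "surgical ablation in the surgical cryoablation group and catheter ablation in the hybrid group".

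Statistical methods plans Fisher's exact test on the proportion free of arrhythmia at 24 months, and also Kaplan-Meier curves, a log-rank test and Cox models.

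**The concern.** The two failure rules and the exemption all refer to the same time, after the 3-month blanking period. They disagree on whether a cardioversion then is an event. The exemption sits in a section on surgical technique and does not appear in the outcome definition, so an analyst could apply either rule and cite the protocol for it.

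The exemption also looks forward. Whether the cardioversion counts depends on rhythm observed later, over a period that is not specified. The patient's status just after month 3 cannot be known then, and if sinus rhythm is lost later, the failure could be dated to the cardioversion or to the relapse.

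The component concerned is not a minor one. Sample size calculation expects the arms to differ in further procedures, antiarrhythmic drugs and cardioversion rather than in final rhythm. If the rule is still open when results by arm are seen, the choice could change the primary result.

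**Working it through.** **1. The readings side by side.** Strict reading: Primary outcome measure and Follow-up as written. Exemption reading: Surgical ablation overrides them. The patients below have no other event.

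| Patient | Strict reading | Exemption reading |
|---|---|---|
| Control, persistent AF at end of blanking, cardioverted, sinus rhythm to month 24 | Failure, about month 3 | Success |
| Control, same, relapse at month 12 | Failure, about month 3 | Failure, dated month 3 or month 12: not stated |
| Hybrid, in AF at the month-3 catheter procedure, cardioverted during it | Not a failure: it happens at that arm's index procedure, before its blanking has run | Same |

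The first row changes the Fisher comparison. The second changes only the time-to-event analyses. The third shows that the hybrid arm has an allowance too, but one without any condition on later rhythm.

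**2. The plan's own sample size.** Inputs from Sample size calculation: 86% hybrid, 50–70% surgery alone, 80% power, 5% level, Fisher's exact test, at least 130 per arm. Sidedness is not stated; two-sided is assumed.

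For 86% v 70%, the mean proportion is 0.78 and the difference 0.16:

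n = [1.96 × √(2 × 0.78 × 0.22) + 0.842 × √(0.86 × 0.14 + 0.70 × 0.30)]² / 0.16²
= (1.148 + 0.484)² / 0.0256 ≈ 104, rounded up to **105** per arm.

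With continuity correction, n/4 × [1 + √(1 + 4/(n × 0.16))]² gives **117**. Exact Fisher power, by enumeration, is 81.7% at 118 per arm and **85.5% at 130**. The stated 130 is not reproduced exactly, but it is on the safe side and is not in question here. The 85.5% is the starting point below.

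**3. Effect of the choice of rule.** Only control patients are reclassified, so hybrid success stays at 86%. The shift in control success is

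(share of controls in persistent AF at end of blanking) × (share of those who stay in sinus rhythm).

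The documents give neither share. As assumptions, 10% × 30% = 3 points and 10% × 50% = 5 points. Shifts of 2 and 10 points are added to show the range. Exact two-sided Fisher power at 130 per arm:

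| Shift in control success | Strict rate 70%, exemption adds | Strict rate 60%, exemption adds | 70% already includes the exemption, strict rule removes |
|---|---|---|---|
| 0 | 85.5% | 99.7% | 85.5% |
| 2 points | 75.8% | not computed | 92.1% |
| 3 points | 69.8% | 98.8% | not computed |
| 5 points | 55.8% | 97.3% | 97.3% |
| 10 points | 20.3% | 85.5% | 99.7% |

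At the 70% planning value, a 3- to 5-point shift reduces the planned 16-point difference to 13 or 11 points.

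**The case against.** **A specific exception overrides a general rule.** On this view Surgical ablation carves out one event at one visit, the other sections state the general rule, and only a cross-reference is missing. That is a fair account of what was probably intended. It does not settle the text: the outcome definition carries no exception, Follow-up says that any need for cardioversion counts, and even as an exception the rule gives no duration for staying in sinus rhythm.

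**The exemption restores balance between the arms.** A reader might infer that control patients get a concession that hybrid patients do not. The documents do not support that. Under Catheter ablation and Follow-up, a hybrid patient's month-3 cardioversion falls at that arm's index procedure and a new blanking period follows. The exemption looks like the control-arm counterpart, and simply deleting it would widen the difference between arms. What remains is narrower: the hybrid allowance is unconditional, while the control one depends on later rhythm.

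**Bias toward hybrid.** A reader might also suspect that the rule flatters the new treatment. It does the opposite, because it raises control success.

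**Loss of power.** Larger assumed shares, such as 20% × 70% = 14 points, give power near 5% from a 70% control rate. That should not be taken as the expected effect. It needs unsupported inputs, the top of the 50–70% range, and 70% being the strict-rule rate. The same 14 points from 60% leave 63.0%, and if 70% already includes the exemption, the strict rule raises power.

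**Event dates are secondary.** This stands for the primary Fisher test: the month-12 relapse is a failure either way. The date matters for the Kaplan-Meier, log-rank and Cox analyses.

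**Conclusion.** The point holds. Primary outcome measure and Follow-up conflict with Surgical ablation over a control-arm cardioversion at the end of blanking, and the conflict extends to the secondary outcome. A control patient who is cardioverted then and stays in sinus rhythm is a failure under one reading and a success under the other. One who relapses later has no determined event date.

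The contradiction rests on the text alone. Its size does not, because the documents do not say how many controls are affected. Assuming a 3- to 5-point shift, 130 per arm, 86% hybrid success and a two-sided 5% test, power falls from 85.5% to 69.8–55.8% if 70% is the strict-rule control rate. It stays at 97% or more from 60%. It rises, to 97.3% at a control rate of 65%, if 70% already includes the exemption. The effect may therefore be material or negligible. The finding is an endpoint with two counting rules, not a demonstrated bias or a demonstrated loss of power.

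**What to change.** Reconcile Primary outcome measure, Secondary outcome measures, Surgical ablation, Catheter ablation and Follow-up into one event-counting rule. Put it in the outcome definition and fix it before any unblinded analysis. The rule should:

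1. state, relative to each arm's index date and blanking period, whether a cardioversion at the end-of-blanking (month-3 post-surgery) assessment counts as an event;
2. not depend on rhythm observed afterwards;
3. date every later arrhythmia or cardioversion on the day it occurs.

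Analyse the other reading as a sensitivity analysis. A single cutoff at 3 months after surgery for both arms would not work: it would turn events inside the hybrid arm's own blanking period, which Catheter ablation tolerates, into failures.

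This changes only how events are counted. Which patients are cardioverted, and when, is unchanged. The cost is wording and one extra analysis, with no new data. The article describes the trial as still recruiting.
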